### Data collection methods: plans to promote participant retention and complete follow-up {25b}

Follow-up assessments at 3, 9, and 18 months will be conducted by researchers at City St George’s, University of London, Warwick University, and Devon Partnership NHS Trust. The study has a dedicated website (https://assuredstudy.co.uk/) and study X feed (@ASsuREDproject) to facilitate engagement with the study.

### Data management {26}

The participant ID will be used on all case report forms (CRFs) for both patient and practitioner participants. Researchers at City St George’s, University of London, Warwick University, and Devon Partnership NHS Trust will enter data into an electronic database. For each researcher, the study team will review the first five case report forms (CRFs) they enter into the database to verify accuracy.

### Statistical methods: primary and secondary outcomes {27a and b}

All analyses will adhere to the intention-to-treat principle unless otherwise stated. The primary outcome (i.e. ED reattendance with a referral to liaison psychiatry within 18 months [a binary outcome—yes or no]) will be analysed using a mixed-effects logistic regression model, with random intercepts for (i) hospital sites (this refers to the different liaison psychiatry teams) and (ii) clinicians. The model will be adjusted for the following factors/covariates: hospital site, a binary indicator of whether the participant presented with suicidal ideation only or evidence of self-harm at baseline, and number of hospital attendances for self-harm/suicidal ideation over the 18 months prior to baseline. Secondary outcomes will be similarly analysed with a mixed-model procedure determined by the nature of the outcome (i.e. whether binary or continuous). Full details of all statistical analyses, including the sensitivity analysis, will be described in a statistical analysis plan (SAP) which will be finalised and signed off before the master database study is locked at study completion. When finalised and signed off, the SAP will be available upon request.

### Statistical methods: handling missing data {27c}

We do not anticipate there will be a significant amount of missing data on the primary outcome given that this is extracted electronically from patient records. Patient characteristics used to stratify randomisation (site and type of presentation, i.e. self-harm or suicidal ideation), which will be included as covariates in the primary analysis, will have been collected in order to implement the randomisation. The primary analysis will include all non-missing data. This approach is valid under the assumption that outcome data are missing at random (MAR) (that is, missingness may be systematically related to covariates included in the model, but not to the missing outcome itself). If more than 5% of primary outcome data are missing, we will conduct sensitivity analyses using methods that may include multiple imputation (with an imputation model that includes predictors of missingness and auxiliary outcome measures that might be associated with the primary outcome) and pattern-mixture modelling to investigate sensitivity to departures from the MAR assumption. This will be described in further detail in the SAP described in the “Statistical methods: methods for additional analyses (e.g. subgroup analyses) {27d}” section.

### Statistical methods: methods for additional analyses (e.g. subgroup analyses) {27d}

In October 2022, the randomisation model was changed from clinician to individual patient randomisation, with the approval of the PSC. A total of 46 patients were recruited under the original study design. As of December 2024, the study achieved its target sample size.

While the components of the intervention have not changed, the timing of delivering the components has changed. In the original study design, the narrative interview and enhanced safety planning components were delivered in the ED, alongside the standard psychosocial assessment. Three solution-focused sessions were then delivered over a period of 8 weeks, and an additional bank session is available up to 9 months after randomisation. Seventeen out of 46 patients recruited under the original study design received the intervention in this form. When individual patient randomisation was implemented, all study participants received the standard psychosocial assessment in the ED, and intervention participants received their first session soon after (rather than in) the ED. All participants in the intervention arm (before and after the study redesign) received the same intervention sessions (one narrative interview and enhanced safety planning session and three solution-focused sessions plus an additional bank session). As such, all participants recruited under both designs will be included in the primary analysis.

The original inclusion criteria focused on patients presenting to the ED with self-harm. Due to increasing numbers of patients presenting with suicidal ideation, inclusion criteria were expanded to include patients with suicidal ideation. While these may be viewed as two distinct presentations, there is considerable overlap between suicidal ideation and self-harm [6, 34], and practitioners highlighted this group as needing further support. People presenting with suicidal ideation may have harmed themselves in the past and re-present to the ED with self-harm. Similarly, people presenting with self-harm may have presented with suicidal ideation in the past and re-present to the ED with self-harm [35]. Both those presenting with self-harm or suicidal ideation have been identified as warranting personalised management plans and active follow-up to reduce the risk of self-harm [6]. As such, the inclusion criteria were expanded to include people presenting with suicidal ideation, meaning the intervention is now being tested on a more heterogeneous sample. A sensitivity analysis will explore the effect of the intervention for participants recruited after the study redesign.

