The present study is part of a research programme called ASSURED which seeks to address this gap in care provision. The overall aim of the ASSURED study is to develop and trial a rapid and cost-effective intervention to improve outcomes for patients presenting to the ED with self-harm and/or suicidal ideation. The ASSURED intervention was developed based on international evidence [14], focus groups, and semi-structured interviews with stakeholders and ongoing input from a lived experience advisory group [11]. The intervention was designed to consist of an enhanced psychosocial assessment in the ED (comprising a narrative interview and enhanced safety plan), three solution-focused follow-up sessions over 8 weeks, a fifth optional session, and three personalised letters sent out over 9 months post-randomisation.

The intervention was tested in a feasibility study and followed by an internal pilot trial, conducted from July 2022 to March 2023 across four NHS hospitals in England with patients presenting with self-harm and/or suicide [15]. The original study was a cluster randomised controlled trial with participating practitioners allocated to ASSURED or treatment as usual (TAU) and the first intervention session taking place in the mental health psychosocial assessment in the ED. However, the Covid-19 pandemic meant ED practitioners’ workload increased significantly, and researchers had no access to ED sites to gain consent from patients before their psychosocial assessment. Hence, the pre-COVID cluster randomised controlled trial had to be modified. The key changes were moving to individual patient randomisation, patient consent soon after ED attendance, and delivering the first intervention session approximately 2 weeks after ED attendance. This removed reliance on ED and liaison staff to screen/consent patients.

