### Outcomes {16}

The primary outcome is a binary outcome [yes (y = 1) or not (y = 0)], i.e. whether study participants re-attend ED and are referred to liaison psychiatry within 18 months from the date of randomisation. Re-attendance with referral to liaison psychiatry is any (a) attendance for self-harm or other mental health crisis, (b) a referral is made and accepted by the liaison team, and (c) the attendance and referral happen in the same ED visit. This data (i.e. date and time of referral to liaison psychiatry after ED attendance) will be obtained from NHS business intelligence teams and may be supplemented/cross-referenced with NHS England. A pre-specified data extraction protocol has been agreed upon with the NHS Business intelligence teams.

The advantage in using this method of data extraction is that the data will be available for almost all participating patients and independent of rater bias. This outcome is linked to Objective A (see the “Objectives{10}” section) and reflects the severity and impact of repeat self-harm and is widely available from routine service data. The extraction of the primary outcome data through the NHS business intelligence teams was partially piloted in the internal pilot phase of the trial [15] and is being validated across participating sites to ensure reliability in the data extraction process.

In addition to the secondary outcomes described below, during the baseline assessment, we collect sociodemographic information for participants on gender, country of birth, ethnic group, physical health conditions, psychiatric diagnosis, previous contact with mental health services, psychiatric hospital admissions, level of education, marital status, type of accommodation, living situation, dependents, employment status, receipt of state benefits, treatment history (including contact with healthcare professionals and general practitioners for self-harm and contact with mental health services), asylum-seeker status, and drug- and alcohol-related problems.

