### Sample size {19}

Around 30% of patients attending the ED with self-harm/suicidal ideation re-attend within 18 months. Reattendance rates are similar for self-harm and suicidal ideation presentations [6]. Reducing this by one-third (i.e. from 30% to 20%) would be a clinically important difference.

The original sample size calculation for the trial was based on a cluster-randomised design with practitioners as clusters. A figure of 0.03 for the intracluster correlation (ICC) was assumed based on published literature [30]. This gave a target sample size of 1088 to achieve 90% power at the 5% significance level, assuming 12 patients in each cluster. When the protocol was amended to individual patient randomisation, we also considered clustering in the intervention arm since practitioners are directly involved in delivering the intervention. However, practitioner-level clustering in a trial of a similar intervention with the same primary outcome was negligible [31, 32], suggesting the original figure of 0.03 for the ICC was an overestimate. The revised calculation (conducted blind to any interim results from the trial) assumed a value of 0.01. With the agreement of the PSC, the power was also reduced from 90% to 80% for the revised calculation, giving a target sample size of 620 (310 in each arm). Due to the impact of COVID-19 (i.e. significantly increased pressure on EDs and diverting mental health patients from EDs), this was a pragmatic decision to address difficulties in recruitment given the challenges of conducting research in addition to clinical care in the ED. The calculation was performed using the “clsampsi” package in Stata (Stata Corporation, College Station, TX, USA) [33]. 

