## Trial status

Practitioner recruitment and training commenced in March 2022 and continued throughout the trial. Patient recruitment commenced in August 2022 and was complete in December 2024. The trial is currently in the follow-up data collection stage, which is scheduled to be complete in the summer of 2026. Currently, the trial is operating under protocol Version 10.0, dated 11.09.2025.

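### The 46 practitioner-randomised patients enter the primary analysis, but the stated model has no term for design phase (minor)

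*Protocol article*

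**What the plan says.** The Background and rationale section {9a} explains that the trial began as a cluster randomised trial in which practitioners, not patients, were allocated to ASSURED or usual care. Section {27d} dates the change to individual patient randomisation to October 2022, reports 46 patients recruited before it, and adds: "Seventeen out of 46 patients recruited under the original study design received the intervention in this form". It argues that intervention participants received the same set of sessions before and after the change, and concludes: "As such, all participants recruited under both designs will be included in the primary analysis".

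The primary model in {27a and b} is a mixed-effects logistic regression with random intercepts for hospital site and clinician. Its covariates are site, presentation type (suicidal ideation only or self-harm) and the number of relevant attendances in the previous 18 months. Design phase is not listed.

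Enrolment also differed. Under the original design consent was taken in the ED before the psychosocial assessment ({32a}). Under the revised design patients are enrolled and randomised within 2 weeks of the visit ({20}). Section {27d} also plans a sensitivity analysis in participants recruited after the redesign.

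**The concern.** Having the same sessions justifies treating the intervention as one intervention. It does not justify treating two allocation mechanisms as one. Three things changed together: the unit of allocation, the time between the ED visit and enrolment, and apparently the share of patients in the intervention arm.

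A covariate distorts an unadjusted comparison when it is associated with both arm and outcome. Phase appears to be associated with arm, since 17 of 46 (37%) received the intervention early on, against a planned 50% later. A link with outcome is plausible. If follow-up starts at enrolment, re-attendances in the first days after the index visit can count for patients enrolled in the ED, but fall before time zero for patients enrolled up to 2 weeks later. The case mix also widened when suicidal ideation was added to the entry criteria, although presentation type is in the model.

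At stake is a small, avoidable bias in the primary estimate, and a primary model that does not follow the way patients were allocated.

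**Working it through.** **Inputs from the protocol article.** 620 patients, 310 per arm; 30% v 20%; ICC 0.01 ({19}). 46 early patients, 17 of whom received the intervention ({27d}).

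**Assumptions.** (a) The 17 who received the intervention are the 17 allocated to it, so the split is 17:29. (b) The 46 are within the 620. (c) The remaining 620 − 46 = 574 split 287:287. The 5% level is taken as two-sided. The 12 patients per practitioner, stated for the original calculation, are carried over to the revised one.

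**Step 1: the plan's own sample size.** The effect is stated as "Reducing this by one-third (i.e. from 30% to 20%) would be a clinically important difference", with 80% power.
- n per arm = [1.960 × √(2 × 0.25 × 0.75) + 0.842 × √(0.30 × 0.70 + 0.20 × 0.80)]² / 0.10² = 293.2, so 294.
- Design effect in the intervention arm = 1 + 11 × 0.01 = 1.11, giving 294 × 1.11 = 326.3, so 327.
- Total = 294 + 327 = 621. Equal arms with only the intervention variance inflated give 618.

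The stated 620 is reproduced and is not in dispute.

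**Step 2: imbalance of phase between arms.**
- Intervention: 17 / (17 + 287) = 17/304 = 5.59%.
- Control: 29 / (29 + 287) = 29/316 = 9.18%.
- Difference: 3.59 percentage points. The early patients are 46/620 = 7.4% of the sample.

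**Step 3: shift in the unadjusted risk difference.** With no treatment effect, shift = 3.59% × (risk gap between phases). The protocol gives no risk gap, so a range is shown.

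| Assumed risk gap | Shift in risk difference |
|---|---|
| 10 points | 0.36 points |
| 20 points | 0.72 points |
| 30 points | 1.08 points |

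If arms of exactly 310:310 are assumed instead, the imbalance is 12/310 = 3.87% and the shifts are 0.39, 0.77 and 1.16 points. Higher early risk would favour the intervention, because more early patients sit in the control arm; lower early risk would work against it.

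**Step 4: scale.**
- Standard error of the risk difference at 30% v 20% with 310 per arm = √(0.21/310 + 0.16/310) = 3.45 points. The Step 3 shifts are 0.10 to 0.31 standard errors.
- With 310:310 arms and a later-phase risk of 30%, early risk between 15 points lower and 20 points higher moves a null odds ratio to between 1.03 and 0.965.
- Two-sided type I error, with null standard error √(2 × 0.21/310) = 3.68 points, is 5.1% for a 10-point gap, 5.5% for 20 and 6.1% for 30.

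**Step 5: the alternative of excluding the 46.** With 287 per arm and the 1.11 design effect, power is 77.1%, against 80.2% at 310 per arm.

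**The case against.** The strongest reply is that most of this is already covered. The clinician random intercept is not restricted to one arm, so it takes up some of the practitioner-level allocation. Prior attendances measure baseline risk directly, and presentation type covers the most obvious change in case mix; {19} says re-attendance is similar in the two presentations. The post-redesign sensitivity analysis isolates the question, the steering committee approved the change, and the Discussion declares the redesign as a limitation. The SAP, which is not shown, may already include a phase term.

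Much of this stands, and it is why the point is minor. What it does not answer is that a random intercept for clinician does not replace a fixed term for a difference between phases. Nor does a sensitivity analysis change the primary estimate.

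The 17:29 split is also open to challenge. The article counts patients who received the intervention, not patients allocated to it. Under simple 1:1 allocation of 46 individuals, 17 or fewer would occur with probability 0.052, so the count does not establish a different intended ratio. For confounding, however, the realised split matters, whatever produced it.

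Two stronger readings are tempting and are not supported:

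- *The outcome window for the 46 opens when their practitioner was randomised.* A reader might infer this because the outcome is whether participants "re-attend ED and are referred to liaison psychiatry within 18 months from the date of randomisation" and only practitioners were randomised at first. But the outcome is defined for participants, and {27d}, describing the original design, places the bank session up to 9 months after randomisation, which makes sense only as a patient-level date. Trial status dates the start of practitioner recruitment and training, not practitioner randomisation, so no loss of follow-up can be calculated. An extraction protocol has been agreed but is not shown, and the index date may be fixed there.
- *Phase confounds the pooled estimate.* Nothing in the article gives re-attendance risk by phase. Without a risk gap, unequal allocation alone does not confound.

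**Conclusion.** The point holds as a minor one. The article pools two allocation designs for a reason that concerns session content only, and the model it states has no design-phase term. Confounding is possible, not shown. Its size is about 0.4 to 1.1 percentage points on the unadjusted risk difference for a phase risk gap of 10 to 30 points, the upper end needing an implausibly large gap. This rests on 17:29 being the allocated split and on the 46 being part of the 620; the article states neither. The covariates already in the model would probably reduce it further. It would not by itself overturn a 10-point effect. The sample size is unaffected.

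**What to change.** Add design phase (original v individual randomisation) as a fixed stratum covariate in the primary and secondary models. Keep the sensitivity analysis in post-redesign participants. In {12}, and when reporting, describe the trial as mainly individually randomised, with 46 patients recruited under practitioner randomisation, and give the number of those 46 allocated to each arm. As a minor clarification, state in one sentence the patient-level index date from which the 18 months run for these 46.

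The cost is one degree of freedom and a few sentences in the SAP. All patients are kept; excluding the 46 would instead lower power from about 80% to about 77%, if they are within the 620. On the article's timetable the SAP is signed off before database lock, with analysts blind until then, so the change can be made without knowledge of results.

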### Economic evaluation

The economic evaluation will follow the intention to treat principle. The aim is to assess the cost-effectiveness of the ASSURED intervention in addition to standard care in comparison to TAU. The primary analysis will be a within-trial cost-utility analysis conducted from the NHS and personal social services (PSS) perspective. The time horizon will be 18 months from randomisation. The primary outcome measure will be quality-adjusted life years (QALYs), derived using CORE-6D—a preference-based measure derived from the CORE-OM instrument [22] and patient survival data. Within-trial cost-effectiveness analysis—with the difference in the number of patients re-attending the emergency department with a referral to liaison psychiatry over the 18-month trial period as an outcome measure—will also be reported.

In sensitivity analysis, QALYs derived using EQ-5D-5L [25] instead of CORE-6D will be reported. The CORE-6D and EQ-5D-5L data will be collected at four assessment points, i.e. baseline and 3-, 9-, and 18-month post-randomisation, using the case report form.

Our cost data collection will cover cost items from the NHS and PSS perspective as well as from a wider societal perspective. The intervention cost will be collected using separate inventory forms for practitioner training and delivery of the ASSURED intervention, respectively. Participant use of inpatient, outpatient, and mental health care will be requested from NHS England. Further data on participant use of primary and community care, medications, social services, and productivity loss and family costs will be collected using the Client Service Receipt Inventory (CSRI), administered at baseline and 3-, 9-, and 18-month post-randomisation.

The economic analysis will recognise the correlation between outcomes and costs data, accounting for clusters at hospital sites and clinicians, and adjusting for key covariates (see “Statistical methods: handling missing data {27c}”). The impact of missing data on outcomes and costs data will be addressed using appropriate methods depending on the pattern and proportion of missing data. The nonparametric bootstrap method will be used to assess uncertainty around summary cost utility measures.

Sensitivity analyses will be conducted including conducting analysis from a societal perspective, using two alternative outcome measures, and evaluating the cost-effectiveness of ASSURED treatment on participants recruited after the protocol change. If the intervention demonstrates a positive effect, we will develop an exploratory analysis evaluating the likely long-term effects of the intervention using a decision analytic model. A detailed health economic analysis plan will be finalised and signed off before the study database is locked and health economists unblinded to intervention allocation.

### Process evaluation—qualitative interviews

We are aiming to conduct a concurrent qualitative process evaluation to explore the implementation and acceptability of the ASSURED intervention and understand the mechanisms of change. We are aiming to conduct interviews with 30 patients, up to 30 practitioners, up to 10 team managers and local PIs with the aim of exploring the delivery of the intervention implementation of ASSURED in the liaison setting, and approximately 10 carers or trusted others if available in the intervention arm across at least 4 sites to capture a range of local contexts. Additional interviews will be conducted with participants in the intervention group who may have experienced difficulties with drug and alcohol use, autistic people, and LGBTQI+ people to further explore their experiences in the ED and with the ASSURED intervention. We anticipate that these interviews will allow full exploration of the implementation, experiences, and context of the intervention. However, if further issues are identified during analysis that require exploration, we will interview additional participants/practitioners. The interviews will explore positive and negative experiences of the intervention.

Interviews will take place face to face or by phone/video conference, depending on the preference of participants. There is potential for these interviews to act as an intervention, so a sensitivity analysis will be carried out excluding those participants who were interviewed.

Participants for the qualitative interviews will be purposively sampled by the study team. Purposive sampling will be carried out based on data collected at post-baseline and the 3-month research interviews. We will identify people of different ages, sex, and ethnicity. The sample will include participants with positive outcomes (completed intervention and/or substantial improvements in self-harm and well-being), negative outcomes (withdrawing from the intervention and/or no reduction in self-harm and well-being), and those with a weak and strong therapeutic alliance.

Intervention practitioners will be purposively sampled to include practitioners of different sex, age, and ethnicity and from different professional backgrounds (e.g. psychiatrists, nurses, social workers, occupational therapists). If practitioners withdraw from the study, we will ask if they are willing to take part in a qualitative interview to explore their reasons for withdrawing.

Carer/trusted other participants, if available, will be purposively selected in the intervention arm to include male and female carers and, based on their relationship with the patient, to include parents, partners, and friends.

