## Data collection, management, and analysis

### Data collection methods: plans for assessment and collection of outcomes {25a}

All potentially eligible patients were approached for consent to join the study after ED attendance. The baseline research assessment took place after consent and prior to randomisation. Participants will be asked to complete further assessments at 3-, 9-, and 18-month post-randomisation. A subsample of approximately 30 patients, up to 30 practitioners, approximately 10 carers or trusted others (if available), and up to 10 team managers and local PIs such as liaison psychiatry team managers will be approached for a qualitative interview to explore experiences of receiving/delivering the intervention. Further details about the interviews are presented under section “Process evaluation—qualitative interviews”.

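### The sensitivity analysis that drops interviewed participants removes people chosen on post-randomisation data, by strong inference from one arm only, so it cannot show whether the interview had an effect

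*Protocol article*

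**What the plan says.** The section on process evaluation by qualitative interviews raises the possibility that the interview acts as an intervention and responds with a fixed rule: "a sensitivity analysis will be carried out excluding those participants who were interviewed".

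The same section says how interviewees are found. On timing: "Purposive sampling will be carried out based on data collected at post-baseline and the 3-month research interviews". On criteria: "The sample will include participants with positive outcomes (completed intervention and/or substantial improvements in self-harm and well-being), negative outcomes", the latter meaning people who left the intervention or did not improve, together with people at both ends of therapeutic alliance. Variety in age, sex and ethnicity is also sought.

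On numbers and arm:
- The core sample is given as "We are aiming to conduct interviews with 30 patients", without an arm attached to the word patients.
- The sentence listing the interview groups ends "if available in the intervention arm across at least 4 sites to capture a range of local contexts", directly after the carers.
- A further set is explicit: "Additional interviews will be conducted with participants in the intervention group". Its size is not given.
- The data collection section (item 25a) says those sampled "will be approached for a qualitative interview to explore experiences of receiving/delivering the intervention".
- The Outcomes section says that only intervention participants complete the alliance scale, at 3 months.

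No interview of control patients, and no matching exclusion in the control arm, is mentioned.

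**The concern.** A sensitivity analysis that removes participants preserves the randomised comparison only if removal is unrelated to outcome within arm, or operates alike in both arms. Here removal depends on early course and adherence after randomisation, which may well be related to 18-month re-attendance, and it appears to operate in one arm only. What remains is a selected intervention group set against a complete control group.

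The outcome window adds a second problem. Re-attendance counts from randomisation, while the selection draws on data up to 3 months. An interviewee who re-attended before the interview already has the event, and the interview cannot have caused or prevented it. The exclusion deletes that event all the same.

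The estimate could therefore shift with no interview effect at all, or stay still because a real interview effect and the selection offset each other. At stake is the reading of this check: it would be reported as robustness evidence on a question it cannot answer.

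**Working it through.** **Inputs.** The Sample size section gives 310 per arm and re-attendance of 30% falling to 20%. The process evaluation section gives 30 core patient interviews. The re-attendance rate among interviewees is not in the document; it is an assumption, shown as a range.

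**The plan's own figure.** Two proportions, 30% versus 20%, two-sided 5%, 80% power:

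n = [1.96 × √(2 × 0.25 × 0.75) + 0.842 × √(0.30 × 0.70 + 0.20 × 0.80)]² / 0.10² = 294 per arm after rounding up.

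With clustering in the intervention arm only, an intracluster correlation of 0.01, and 12 patients per practitioner (carried over from the cluster-design calculation as an assumption), the design effect is 1 + 11 × 0.01 = 1.11, or 1.055 averaged over the arms. Then 2 × 294 × 1.055 = 620.3, which reproduces 620. That figure is not in dispute; it supplies the 310.

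**Which arm.** For the additional interviews the arm is stated. For the core 30, three things point to the intervention arm: the interviews concern receiving or delivering the intervention; a control patient can neither complete nor leave it; and alliance exists only for intervention participants.

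**Share removed.** 30 / 310 = 9.7% of the intervention arm and none of control, leaving 280 versus 310.

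**Effect on the estimate.** Let p be the intervention arm's rate, q the interviewees' rate and k the number interviewed.

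Remaining rate = (310p − kq) / (310 − k)

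Shift = k(p − q) / (310 − k)

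With k = 30 the multiplier is 30 / 280 = 0.107, so each 10-point gap between q and p moves the risk difference by about 1.1 points. It is zero when q = p.

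Design effect present (62 intervention events in 310; control 30%):

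| Assumed q | Events removed | Remaining rate | Difference from control |
|---|---|---|---|
| 10% | 3 | 59/280 = 21.1% | 8.9 points |
| 20% | 6 | 56/280 = 20.0% | 10.0 points |
| 30% | 9 | 53/280 = 18.9% | 11.1 points |
| 40% | 12 | 50/280 = 17.9% | 12.1 points |

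No true effect (93 intervention events in 310; control 30%):

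| Assumed q | Remaining rate | Apparent shift | Odds ratio |
|---|---|---|---|
| 10% | 90/280 = 32.1% | +2.1 points | 1.11 |
| 30% | 84/280 = 30.0% | 0 | 1.00 |
| 50% | 78/280 = 27.9% | −2.1 points | 0.90 |

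None of these rows contains an interview effect; every shift comes from selection alone.

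**The case against.** The strongest reply is that little is at risk. Intention to treat is the stated default, the primary analysis uses all non-missing outcomes, and nothing lets the exclusion analysis replace that result. This stands: the primary conclusion is not touched.

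Second, the sampling deliberately takes both good and poor courses and both weak and strong alliance. Opposing selections may partly cancel, and if interviewees re-attend at their arm's overall rate the shift is zero. This also stands. A reader might infer that the exclusion is bound to bias the result, or bias it one way. The document does not support that: it gives no link between the selection criteria and re-attendance and no interviewee rate. Cancellation would nevertheless be luck, since nothing in the plan secures it.

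Third, the arm of the core 30 is not stated outright. The closing reference to the intervention arm can be read as applying to carers alone, a restriction the section later repeats for carers. So one-arm origin is a strong inference for these 30, and fact only for the additional interviews.

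Fourth, a reader might infer a much larger distortion because further interviews are allowed. No number is given for them, so any larger total is a guess; the working stays with the stated 30.

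Finally, details of sensitivity analyses are left to an analysis plan that is not shown and may add caveats. But the article already fixes who is excluded, and an analysis plan that implements this faithfully inherits the problem.

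**Conclusion.** The point holds as a defect in one sensitivity analysis. Excluding interviewees conditions on post-randomisation data, by strong inference in one arm only, and discards pre-interview events. It can introduce selection bias in either direction, and its result cannot be read as evidence for or against an interview effect.

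The size is modest at the stated number of interviews: about 1.1 points of risk difference per 10-point gap in rates, so 8.9 to 12.1 points around the planned 10 for assumed interviewee rates of 10% to 40%. This rests on 310 analysed in the intervention arm, all 30 interviewees belonging to it, and assumed interviewee rates. It is worth correcting before the analysis plan is signed off, but it does not threaten the primary intention-to-treat result.

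**What to change.** Replace the simple exclusion with an analysis that keeps all randomised participants:

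- Retain every re-attendance by an interviewee that occurred before the interview.
- For interviewees with no event by then, treat later status as missing and multiply impute it. Use arm, baseline covariates, 3-month measures, pre-interview re-attendance and all the variables that drove selection, including completion of or withdrawal from the intervention and, within the intervention arm, alliance.
- State that this assumes later status is missing at random given those variables.
- Confirm that interview dates are recorded. The article does not say so, nor when interviews take place, so the amount of follow-up to be imputed is unknown.
- State the arm of the core 30 explicitly.

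If the exclusion analysis is kept, label it non-randomised and exploratory, and do not present it as evidence of robustness. The intention-to-treat analysis stays primary either way.

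The cost is a short passage in the analysis plan, a little extra programming, and reliance on a missing-at-random assumption. The article schedules follow-up to run to summer 2026 and requires the analysis plan to be signed off before database lock, so the change can be made at sign-off.
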